##### Session Outcomes: Self-reflection Survey

In the 3 implementation countries, session outcomes, as possible change mechanisms, will be measured by a questionnaire with a 5-item short version based on the Bern Patient Questionnaire [49]. This measure includes the rating of the overall helpfulness of the module and the matching of participant’s needs and presented content, as well as gains in self-esteem, mastery experiences, and insight. Items are rated on a scale ranging from 3=not at all to 3=yes, exactly. Participants will be asked to complete the session outcomes items (self-reflection survey) after the completion of each submodule or module. In addition, these items related to the whole intervention will be assessed after the intervention.

#### Mood Monitoring

In the 3 implementation countries, mood monitoring will be measured by the mood self-check tool developed for this intervention, which assesses grief and depression symptoms, social withdrawal, and perceived progress within the intervention. Starting from the beginning of the web-based self-help intervention, the program will trigger an automatic message every other week asking participants to complete the mood self-check. Although this mood self-check is not part of the evaluation, it will inform the guidance of participants.

#### User Satisfaction

In the 3 implementation countries, user satisfaction will be measured by the Patient Satisfaction Questionnaire adapted for web-based interventions [50,51]. The Patient Satisfaction Questionnaire is a self‐report measure that explores patients’ overall satisfaction with the treatment. It includes 8 items that are rated on a 4‐point scale from 1=low satisfaction to 4=high satisfaction.

#### Use Data

Adherence will be measured through use, which will consist of the number of log-ins, completion of modules and submodules, and visits to the program’s pages. Use data will be assessed continuously while using the self-help program.

#### Context Measures and Sociodemographic Variables Assessed at Baseline

Context and predictor variables include age, gender, education, nationality, marital status, duration of relationship until the loss, time since the loss, and details about the loss (death due to illness, violence, suicide, or accident). These data will be collected in the 3 implementation countries.

#### Technology Acceptance

The trial conducted in the Netherlands is aimed at thoroughly investigating the technology acceptance of the intervention, specifically focusing on perceived usefulness (self-devised) and effort expectancy (based on the study by De Veer et al [52]), measured at baseline. The usability (based on the study by Holden [53]) and user experience using the AttrakDiff instrument (User Interface Design GmbH) [54] will be assessed midintervention. Finally, after the intervention (week 10), usability and user experience will be measured again, and participants will be asked to complete a measure of acceptance (self-devised) and effort (based on the study by De Veer et al [52]). In addition, at this phase, we will add open questions to assess the use and appreciation of mood self-check monitoring and respective feedback messages and critical incidents. As a follow-up, focus groups will be conducted to better understand the perceived benefit of the web-based self-help program. Focus groups will address usability and technical acceptance, answer which intervention elements need improvement, and assess the potential use of the intervention in daily and working routines.

The research team agreed to share all the materials used in the study, including the scales used (if open access) and the focus group scripts upon request to the corresponding author.

### Data Collection, Management, and Analyses

Data will be assessed using web-based questionnaires programmed in REDCap (Research Electronic Data Capture; Vanderbilt University) [55,56] or Qualtrics (Qualtrics) [57]. Data integrity will be enforced according to referential data rules, valid values, range checks, and consistency checks. Checks are applied at the time of data entry into a specific field. In addition, data on the use of the self-help sessions are collected within the platform. All data will be saved in an anonymous manner, only identified by a code that is not related to the participant’s identity. Data will be divided over 3 databases, an anonymized database containing data entered by the user into the platform (eg, exercises), an anonymized database containing use data logs, and a database that contains personal identifiers and the link to the internal anonymized identifier. After the end of the study, the last database will be deleted so the complete data set is anonymous. The platform and all data will be stored on International Organization for Standardization 27001–certified servers and will make use of secured connections. All data will be treated according to the guidelines of Dutch law and good clinical practices of the Swiss Federal Act on Research Involving Human Beings. Only the researchers directly involved in the study will have access to the data. Finally, it is important to note that this research collects data that allow identification of severe distress or mental health symptoms, including suicidal ideation. Following the public health guidelines on the management of personal data collection, this intervention is designed to flag the participants who show suicidal ideation or severe mental health crises that can be addressed in the guidance.

### Statistical Analyses

Dropout is defined as participants who withdraw actively from the study after randomization or fail to fill out the postintervention questionnaires despite 2 reminders. For technology acceptance, noncompliance is defined as not filling out the biweekly mood self-check questionnaire despite 2 reminders. Noncompliant participants are also defined as those who, despite not actively quitting the study, do not complete the 2 mandatory study modules (module 1 and module 2) within 10 weeks. Nevertheless, these participants will be a part of the intention-to-treat analysis, as they have been randomized. Adherence will be assessed with the number of modules completed and use data.

All rating scales will be checked for reliability (Cronbach α) and multicollinearity (correlation analysis). Results will be reported on scale averages, as well as multiple 2-way correlations. Analyses will be conducted according to the intention-to-treat paradigm. First, we will analyze the extent of missing data, explore the missing data patterns, and determine the type of missing data (missing completely at random, missing at random, or not missing at random). If the missing mechanism is missing at random, multilevel mixed effects regression analyses will be used, which allow a different number of measurement points per participant and are thus less sensitive to missing data.

Multilevel mixed effects models with repeated measures data will be conducted to evaluate the efficacy of the intervention after 10 weeks and the stability of the effects after a further 10 weeks. Restricted maximum likelihood estimation will be used, which is recommended for small group samples and yields asymptotically efficient estimators for balanced and unbalanced designs. Mixed effects models have several advantages. These consider the dependency of the data and account for the correlation of the repeated measures within individuals. Furthermore, mixed effects models use all available data of each participant and estimate parameters of missing values. Models for each outcome variable will be computed. The pre-post comparisons of all outcome measures will include time as a within-group variable, the intervention format as a between-group variable, and an interaction term time by a group for cross-level interactions. To test the stability of the effects from the postintervention period to follow-up, only time will be included as a within-group factor in the mixed effects models. Cohen *d* will be calculated as effect size for all observed outcome variables. Furthermore, a Reliable Change Index will be computed as a measure of clinical change. Complementary analyses will test whether variables such as age, time since loss, and the severity of grief symptoms have an effect on the outcome by including them as predictors in the regression models. To analyze the longitudinal interplay of predictor variables and test mediation analyses, structural equation models will be conducted. Analyses will be conducted using SPSS Statistics (IBM) [58] and Mplus [59] software.

To explain technology acceptance, a backward regression analysis will be conducted. All qualitative data will be analyzed thematically, following the guidelines by Braun and Clarke [60], whereas reporting will be done according to the consolidated criteria for reporting qualitative research standards [61].

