### Sample Size

Sample size was determined by a power analysis based on a probability level of 0.05 and a power of 0.80 with G*Power [36], which is based on the results of the evaluation of LIVIA [14]. As in LIVIA, we expected a large effect size of Cohen *d*>0.80 for the decrease in grief as primary outcome, measured by the Texas Revised Inventory of Grief (TRIG), in the comparison of the intervention with a waitlist control group or care-as-usual control group. For the comparison of the standardized intervention with the self-tailored interventions, we expect a small to moderate effect (Cohen *d*=0.30) in favor of the self-tailored version. Power analyses for a repeated measures ANOVA with a within-between interaction for 3 groups in Switzerland estimated a sample size of at least 85 participants. For the 2-arm designs in Portugal and the Netherlands, we anticipate a dropout rate of 15% and, consequently, efforts will be made to recruit more primary end users than indicated by the power analysis.

For the target group of primary end users, older mourners, the aim is to include at least 85 participants in the study conducted in Switzerland with an allocation of 35:35:15 for the 2 active arms and the waitlist control group, respectively; at least 80 participants in Portugal with an allocation of 40:40; and at least 40 participants in the Netherlands, with an allocation of 20:20.

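### The pre-post efficacy model estimates a difference in change scores; adjusting for the baseline TRIG already collected would be more precise, by an amount that depends on an unstated correlation

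*Protocol article*

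**What the plan says.** The Statistical Analyses section specifies mixed effects models for repeated measures, fitted by restricted maximum likelihood. "The pre-post comparisons of all outcome measures will include time as a within-group variable, the intervention format as a between-group variable", together with a time-by-group interaction. No baseline covariate and no constraint of equal baseline means is named. Stability from post-intervention to follow-up is tested with time only. Age, time since loss and grief severity enter as predictors in complementary analyses, which the Main Research Hypotheses section calls exploratory.

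Under Overview and Measurement Times, primary and secondary outcomes are measured at baseline and at 10 weeks in every arm of all three trials. Time since loss is also collected at baseline ("time since the loss, and details about the loss").

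On size, the Sample Size section says: "Sample size was determined by a power analysis based on a probability level of 0.05 and a power of 0.80" and "we expected a large effect size of Cohen *d*>0.80 for the decrease in grief as primary outcome". The planned arms are small in two trials: Switzerland "with an allocation of 35:35:15 for the 2 active arms and the waitlist control group", and 20:20 in the Netherlands. The third is larger: "at least 80 participants in Portugal with an allocation of 40:40". Dropout of 15% is anticipated for the two-arm trials.

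**The concern.** When baseline and week 10 are both outcomes and group has a free main effect, the time-by-group coefficient is the difference between arms in mean change. Randomization gives more information than that: before treatment, the arms are samples from one population with one baseline mean. An analysis that uses this fact (baseline as covariate, or one common baseline mean) estimates the same treatment effect and, in large samples, is never less precise.

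Precision is scarce here, with a 15-person Swiss waitlist and 20 per arm in the Netherlands. In arms of that size chance baseline differences are likely, and a change-score contrast carries them into the estimate through regression to the mean. The data needed to do better are already scheduled.

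**Working it through.** **The plan's own figure.** The Swiss size comes from a "repeated measures ANOVA with a within-between interaction for 3 groups in Switzerland estimated a sample size of at least 85 participants". The G*Power formula is λ = f²·N·m/(1−ρ), with df₁ = (k−1)(m−1) and df₂ = (N−k)(m−1). Take k = 3 and f = d/2 = 0.15 for the format comparison. Then N = 111 with m = 2 and ρ = 0.5, or 89 at ρ = 0.6; with m = 3, N = 91 at ρ = 0.5, or 74 at ρ = 0.6. The article gives none of ρ, m and f, so 85 cannot be rebuilt. This does not affect the present point, but it confirms that ρ has to be assumed.

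**Inputs.** From the Sample Size section: α = 0.05 (sidedness not stated; two-sided used), d = 0.80 against control, d = 0.30 between formats, and the arm sizes above. Assumed: ρ from 0.3 to 0.8, equal variances over time, and d expressed in raw TRIG standard deviations.

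**Variance, complete pre-post data.**
- Planned contrast: 2σ²(1−ρ)(1/n₁ + 1/n₂).
- Baseline-adjusted: σ²(1−ρ²)(1/n₁ + 1/n₂).
- Ratio, adjusted to planned: (1−ρ²)/[2(1−ρ)] = (1+ρ)/2, a reduction of (1−ρ)/2.

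| ρ | planned 2(1−ρ) | adjusted 1−ρ² | reduction |
|---|---|---|---|
| 0.3 | 1.40 | 0.91 | 35% |
| 0.5 | 1.00 | 0.75 | 25% |
| 0.7 | 0.60 | 0.51 | 15% |
| 0.8 | 0.40 | 0.36 | 10% |

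Comparing week-10 scores alone has variance 1.00 on this scale. The planned contrast therefore equals a post-only comparison at ρ = 0.5, is worse below that value and better above it.

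**Power.** Noncentral t with n₁ + n₂ − 2 degrees of freedom and noncentrality d/[s√(1/n₁ + 1/n₂)], where s is the square root of the planned or adjusted entry in the table. Example, Netherlands at ρ = 0.5: √(1/20 + 1/20) = 0.316; planned 0.80/0.316 = 2.53, adjusted 0.80/(0.866 × 0.316) = 2.92; on 38 df these give 69% and 81%.

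| Comparison | ρ | planned | adjusted |
|---|---|---|---|
| Netherlands 20:20, d = 0.80 | 0.3 | 55% | 73% |
| | 0.5 | 69% | 81% |
| | 0.7 | 89% | 93% |
| | 0.8 | 97% | 98% |
| Switzerland 35 v 15, d = 0.80 | 0.5 | 72% | 84% |
| Portugal 40:40, d = 0.80 | 0.5 | 94% | 98% |
| Swiss formats 35:35, d = 0.30 | 0.5 | 24% | 30% |

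With 15% loss in the Netherlands (17:17), ρ = 0.5 gives 62% and 74%. A normal approximation gives values about 2 points higher in the Dutch case (71.6% and 83.2% at 20:20), with the same gain.

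**Finite-sample check.** In simulation (4,000 runs) at ρ = 0.5 and arm sizes 40:40, 20:20 and 15:35, the variance reduction is about 23% with complete data and 19% to 21% with 15% of week-10 values missing.

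**The case against.** The strongest reply is that nothing here is invalid and that adjustment terms are the sort of detail an article leaves to an analysis plan. The first half stands: under randomization the planned contrast is unbiased, and sensitivity to chance imbalance is not bias. The second half does not, because the article states the terms of the model, and the stated form is the less efficient one. The complementary predictor analyses do not change this, since they are not the efficacy model.

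The size is also open to challenge, and rightly. A reader might infer that the baseline precision is simply thrown away, or that adjusting is worth 13 extra Dutch participants (40 × 1.33 = 53). Both readings rest on ρ = 0.5, which is nowhere in the article. Above 0.5 the change score keeps part of the gain. The equivalent is about 7 participants at ρ = 0.7 (40 × 1.18 = 47) and 4 at 0.8 (40 × 1.11 = 44). At ρ of 0.7 or more the planned Dutch contrast already exceeds 80% power for d = 0.80.

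Two further inferences fail. One is that an adjusted group difference at week 20 should also be primary. In Switzerland and the Netherlands the waitlist starts the program at 10 weeks, so its week-20 measure follows treatment. The other is that time since loss must enter the efficacy model. It is collected and plausibly prognostic, but no figure shows what it would add once baseline TRIG is used, and the plan already examines it as a predictor.

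Last, a common baseline mean requires that baseline be unaffected by allocation, and the trials are unblinded. The Randomization section puts the Swiss baseline questionnaire before allocation. For the Netherlands and Portugal the order is not explicit.

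**Conclusion.** The point holds as one of efficiency, not validity. For any ρ below 1, baseline adjustment has the smaller large-sample variance, by (1−ρ)/2: 35% to 10% over ρ from 0.3 to 0.8, and somewhat less at these arm sizes with 15% dropout. It matters most in the Netherlands and for comparisons with the 15-person Swiss waitlist. At ρ = 0.5 and complete data, the planned contrast misses the 80% target in the Netherlands and in Switzerland (35 v 15), and the adjusted one meets it. In Portugal the gain is small at that ρ, and the comparison of the two formats stays underpowered either way. These power figures assume d = 0.80 (0.30 for formats) on the raw TRIG scale and equal variances; ρ is an assumption throughout. The change should be made because it costs almost nothing, not because the planned test would mislead.

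**What to change.** State that the treatment effect is the week-10 difference between arms in TRIG, and likewise for the secondary outcomes. Estimate it in one of two ways:
- The same restricted maximum likelihood mixed model with a common baseline mean across arms. This keeps participants who have baseline data only, in line with the intention-to-treat aim. Use it only where baseline is measured before allocation: the Randomization section shows this for Switzerland; confirm it for the Netherlands and Portugal.
- The week-10 outcome with baseline score as covariate. Participants without a week-10 value then contribute no outcome.

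In Switzerland and the Netherlands, limit the randomized group contrast to week 10 and keep the existing time-only analysis for follow-up. A time-since-loss covariate is not a required part of this change.

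The cost is a few sentences in the analysis section and a check of the order of baseline and allocation. No new data are needed, and the software already named can fit these models.

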### Randomization

All eligible participants are randomly assigned to the active arm of the study (including the 2 active arms, standardized or self-tailored intervention format for the trial in Switzerland) or to the control or care-as-usual groups, depending on the implementation country. Participants assigned to the active arms will receive a participant code that gives them access to the self-help program and will be asked to use it for 10 weeks. Participants in the waitlist control group will start using the program 10 weeks after randomization. In Portugal, participants in the care-as-usual group can use the program after 20 weeks of follow-up, if requested.

For the 3 trials, the block-wise randomization was performed by an external programmer not involved in the trial using a random allocation sequence. The trials are unblinded. In Switzerland, the participants register on the study website and fill out the baseline questionnaire. Then, a member of the study team conducts the screening telephone call and allocates the participants to the 3 arms based on randomization numbers provided by the external programmer. In the Netherlands and in Portugal, participants are directly contacted by the teams responsible for implementing the study. Contacts are made based on their own professional lists. In the 3 countries, participants receive the intervention link after their eligibility has been confirmed in a phone call or an individual interview, depending on the implementation country.

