### Measures

#### Overview and Measurement Times

All clinical outcomes are self-report measures and will be completed on the web or within the program. In the trials conducted in Switzerland and the Netherlands, for the active arms, measurements of primary and secondary outcomes will take place (1) before users start using the program at baseline; (2) after the intervention, 10 weeks after the start of the program; and (3) at follow-up, 20 weeks after the user starts the program, which will measure the stability of the outcomes over time. For the waitlist control groups, the measurement times will occur at baseline (week 0), after 10 weeks waiting to start the intervention, after completing the intervention (week 20), and at follow-up (week 30). In the trial conducted in Portugal, the active arm and control group, care as usual, will occur at baseline, 10 weeks after starting the intervention, and at follow-up, 20 weeks after starting the intervention.

As no cross-cultural comparisons are planned, measures will be adapted to each country’s trial. The measures used in the 3 different countries depend on the measures available for each language, which will result in the use of equivalent measures when it is not possible to use the same. Primary and secondary outcomes will allow for testing the efficacy.

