## Discussion

### Expected Findings

In 3 different trials, the present research expects to test the efficacy of a web-based self-help grief intervention for older mourners. Specifically, we expect that the intervention decreases grief symptoms, as well as depression symptoms and perceived loneliness after completing the intervention when compared with the control group. These outcomes are expected are to be stable at follow-up. Moreover, the trial in Switzerland will test the hypothesis that the self-tailored delivery format, by providing participants the opportunity to meet their specific needs at each moment, leads to better outcomes and to higher satisfaction with the intervention than the standardized intervention. In the trial conducted in the Netherlands, the results of this study will also provide insights into the acceptability of web-based self-help interventions directed at older adults who are affected by grief symptoms, psychological distress, or adjustment problems in daily life after the loss of their partner, as well as insights into the prevention of prolonged grief. Finally, in the trial conducted in Portugal, the cost-effective and qualitative analyses of the barriers to using the intervention, will provide insights on how to redirect the resources used to implement it.

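### The follow-up stability test has time as its only factor, so it cannot show whether the effect against care as usual in Portugal, or the Swiss format difference, is maintained at week 20

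*Protocol article*

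**What the plan says.** The Statistical Analyses section describes two models. The pre-post model contains time, "the intervention format as a between-group variable, and an interaction term time by a group for cross-level interactions". For the later period the group term goes: "To test the stability of the effects from the postintervention period to follow-up, only time will be included as a within-group factor". The section does not separate the countries here, so the rule applies to all three trials.

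The design gives different material at week 20 in each trial:

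- **Portugal.** Under Overview and Measurement Times, assessments in "the active arm and control group, care as usual, will occur at baseline, 10 weeks after starting the intervention, and at follow-up, 20 weeks" after the start. Under Randomization, "participants in the care-as-usual group can use the program after 20 weeks of follow-up, if requested".
- **Switzerland and the Netherlands.** Active arms are assessed "at follow-up, 20 weeks after the user starts the program, which will measure the stability of the outcomes over time". Waitlist participants start the program at week 10 (Randomization).

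The Expected Findings section first describes the expected reductions as relative to the control group and then adds: "These outcomes are expected are to be stable at follow-up". No margin, interval or other criterion for stability is given.

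**The concern.** The effect described under Expected Findings is a difference from control. A model with no group term contains no such difference and cannot say whether it lasts.

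This matters here because grief changes without treatment. The Background section says that for most bereaved people grief eases within weeks to months, and the Participants section admits people from one month after the loss. Weeks 10 to 20 may therefore include natural recovery in every arm. A flat course in the active arm can hide a shrinking advantage over control, and a falling course can accompany an advantage that is fully kept.

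Portugal is the only one of the three trials with an untreated randomized comparison at week 20, and the stated efficacy analysis has no term for it. The Swiss format comparison at week 20 is omitted in the same way. At stake is the claim that the effect is maintained.

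**Working it through.** The protocol gives no figure for the follow-up analysis, so there is none to reproduce.

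**Inputs from the protocol (Sample Size).** Two-sided alpha 0.05 (sidedness is not stated and is assumed). Portugal 40:40, with 15% dropout anticipated: 40 × 0.85 = 34 per arm, taken as the number present at week 20. Swiss active arms 35:35. Expected effects: d = 0.80 against control (the text says greater than 0.80) and d = 0.30 between formats.

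**Inputs that are assumptions.** Correlation between weeks 10 and 20 (rho) of 0.6 to 0.7; a rebound of 0.3 SD; control recovery of 0.4 SD. None of these is in the protocol.

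**1. Which contrasts exist at week 20**

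| Contrast | Randomized and uncontaminated at week 20? | In the stated follow-up model? |
|---|---|---|
| Portugal, standardized v care as usual | Yes | No |
| Switzerland, self-tailored v standardized | Yes | No |
| Switzerland and Netherlands, active v waitlist | No, waitlist treated from week 10 | Not applicable |

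**2. What the time term measures.** In the active arm the change from week 10 to week 20 equals the change in control plus the change in the between-group effect. Suppose the effect is 0.8 SD at week 10, controls then improve by 0.4 SD, and the effect falls to 0.4 SD. With improvement counted as positive, active-arm change = 0.4 + (0.4 − 0.8) = 0. The time test in that arm is then non-significant in 95% of trials, although half the effect has gone. At 40 per arm, group-by-time would detect the loss with power 0.42 (rho 0.5) to about 0.62 (rho 0.7).

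In the opposite case both arms improve by 0.4 SD and the effect is fully kept. At 40 per arm and rho 0.7, the active-arm time test is significant in 89% of trials and group-by-time in 5%. The time test can therefore mislead in either direction.

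**3. A non-significant time term as evidence of stability.** The SD of change is √(2(1 − rho)): 0.894 at rho 0.6 and 0.775 at rho 0.7. The noncentrality for a 0.3 SD rebound at n = 34 is 0.3 × √34 / SD of change, which is 1.96 and 2.26. Against a critical t of 2.03 on 33 degrees of freedom, the probability of a non-significant result is 0.52 and 0.41.

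A Swiss model with no group term would pool the two formats. The same calculation gives 0.28 to 0.16 at n = 60 and 0.21 to 0.11 at n = 70.

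**4. What the omitted week-20 contrasts could deliver (unadjusted, SD units)**

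- Portugal 34:34: SE = √(2/34) = 0.24. The 95% CI is about ± 2.00 × 0.2425 = ± 0.48. Power at d = 0.80 is 0.90 (0.94 at 40:40).
- Swiss formats 35:35, no dropout: SE = √(2/35) = 0.24. Power at d = 0.30 is 0.24; 175 per arm would be needed for 0.80.

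**The case against.** Five points can be made for the plan.

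- **Efficacy is fixed at week 10.** The outcome definitions use week 10, that analysis has group and group-by-time, and none of the listed hypotheses concerns follow-up. This stands. A reader might infer that the efficacy analysis itself is compromised; it is not.
- **No rule equates non-significance with stability.** A reader might infer that the authors will read p > 0.05 as a maintained effect. The protocol does not say so, and it also plans Cohen d and a Reliable Change Index. What can be said is that no criterion is stated, which leaves that reading open.
- **Stability may mean within-arm stability.** The measurement section speaks of outcomes over time, which a time term does address. But that phrase concerns the Swiss and Dutch active arms, while the analysis section speaks of effects and Expected Findings refers to control. The wording is inconsistent, and the within-arm reading does not answer the comparative question.
- **The week-20 data are used elsewhere.** A reader might infer that the Portuguese comparison is thrown away. The Cost-effectiveness Analysis section plans incremental ratios per point of grief over the follow-up period, which implies a between-arm difference. That analysis is exploratory and states no clinical week-20 estimate with its own interval, so the gap is in the efficacy analysis only.
- **Time alone suits the waitlist contrasts, and the Swiss format contrast has little power.** Both stand. It would also be wrong to quote error rates for a single small Swiss or Dutch arm as the cost of an omitted contrast: the Dutch trial has no untreated control at week 20, and the Swiss model as written pools the formats.

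**Conclusion.** The point holds for the maintenance claim. As written, the follow-up model cannot show whether the effect against care as usual in Portugal, or the difference between the Swiss formats, persists to week 20, although both randomized comparisons are measured then. That conclusion follows from the text alone and needs no numerical assumption.

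The size does rest on assumptions. A halving of the effect, from 0.8 to 0.4 SD, would leave the active arm flat if controls recovered 0.4 SD. A 0.3 SD rebound would go undetected with probability 0.41 to 0.52 in 34 participants at rho 0.6 to 0.7, so a non-significant time term alone is weak evidence of stability. The Portuguese contrast is worth having: SE about 0.24 SD and power 0.90 at the plan's own d of 0.80. The Swiss one supports an estimate and interval only. This should be fixed, but it does not threaten the week-10 result.

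**What to change.** - **Portugal and the two Swiss active formats.** Fit baseline, week 10 and week 20 in one mixed model with group, time and group-by-time. Report the week-20 between-group difference with its 95% CI. In Portugal this is the maintenance result. For the Swiss formats give the estimate and CI without a claim resting on significance.
- **Swiss and Dutch intervention-versus-waitlist question after week 10.** Report the within-arm change from week 10 to week 20 with its CI and label it uncontrolled.
- **Throughout.** Say whether stability refers to the within-arm outcome or to the between-group effect, and do not infer it from p > 0.05.

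The cost is a change of wording in the analysis section or analysis plan and one extended model per outcome. No new data, visits or participants are needed.
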